### PUMP: PEEP adjustment and monitoring procedure

PUMP is a regular mini-recruitment manoeuvre procedure designed to adjust PEEP based on patient-specific changes in condition. This mini-RM is also guided by CURE software and moves between ±4 cmH_2_O from the current PEEP. PUMP should be performed twice daily during normal working hours (0800–1800 hours) or at any other time if lung de-recruitment is considered to be the likely cause of new desaturation. The Pi will be left the same as in the current ventilator settings. To ensure a PUMP can be safely carried out, the RM checklist and preparation steps are to be followed. If the checklist preconditions are met, the PUMP may be carried out.

The following instructions are given to the clinician:
Titrate sedation so the patient is not verbally responsive and has loss of their eyelash reflex. Use fentanyl or morphine increments with propofol to provide a “balanced” deeper sedation level. Give rocuronium 0.5–1.0 mg/kg through a reliable i.v. line; ensure the line is flushed.Set the ventilator to SIMV-PC mode with the appropriate aforementioned settings.Reduce the PEEP to 4 cmH_2_O less than the current PEEP setting. The CURE software cannot estimate an optimal PEEP that is lower than the current PEEP setting.Start PUMP on the CURE soft programme.Follow the steps of the CURE soft PUMP protocol. During the PUMP procedure, increase PEEP in two steps of 4 cmH_2_O. Then decrease PEEP in two steps of 4 cmH_2_O (you may need to adjust the FiO_2_ to keep the SpO_2_ ≥ 90%).Once you have returned PEEP to the starting PEEP level (initial PEEP − 4 cmH_2_O), perform a second PUMP using the same method described in point 5.The CURE soft programme will recommend a new PEEP at the end of the second PUMP. You may either accept this computerised recommendation, or reject it (with a reason) if you feel the new PEEP level is inappropriate. If rejected, record your reason(s) on the programme.Return the patient to the previous ventilation mode.Adjust to V_T_ ≤ 6–8 ml/kg IBW. If the plateau pressure is > 30 cmH_2_O, adjust the V_T_ down to 4–6 ml/kg IBW and tolerate permissive hypercapnia. Also ensure that the DP remains ≤15 cmH_2_O. You may increase the respiratory rate up to 30 breaths/min provided there is no significant auto-PEEP causing breath stacking.Reduce the ETT cuff pressure to the previous level and re-set ventilator alarms to previous settings.Take an ABG 30 to 60 mins following the conclusion of the procedure

### Standard practice SRM

Participants assigned to SPV have PEEP determined using clinical judgement, as per local unit standard care. However, if oxygen requirements are high or have recently increased e.g. an FiO_2_ ≥ 50% to keep SpO_2_ in the target range of 93–95%, the following should be considered if the treating clinician is intending to carry out an SRM:
Patient conditions for which lung recruitment are contraindicated are excluded (e.g. endobronchial intubation, mucous plugging, pneumothorax etc.)Analgesia and sedation, and patient position have been optimisedSmall changes to respiratory rate, V_T_, pressure support or neuromuscular blockade to optimise mechanical ventilation

If the oxygenation does not improve with the aforementioned interventions, then PEEP may be increased in increments of 2 cmH_2_O. If the PEEP is ≥ 15 cmH_2_O and FiO_2_ is ≥ 60%, (P/F ~ 100) in spite of addressing the aforementioned points, a staircase recruitment manoeuvre (SRM) may be considered if the clinician feels this is in the best interests of the patient.

The SRM procedure does not utilise the CURE software to perform recruitment and therefore the software will not guide the user, nor make any PEEP suggestions. The software will still record airway pressure and flow through this procedure.

To ensure a SRM, can be safely carried out, the RM checklist and preparation steps are to be followed. If the checklist preconditions are met, the SRM may be carried out (note, the SRM procedure does not utilise CURE software to perform recruitment).

The following instructions are given to the clinician:
Titrate sedation so the patient is not verbally responsive and has loss of their eyelash reflex. Use fentanyl or morphine increments with propofol to provide a “balanced” deeper sedation level. Give rocuronium 1.0–1.5 mg/kg through a reliable i.v. line; ensure the line is flushed.Set the ventilator to SIMV-PC mode.Set Pi to 15 cmH_2_O above PEEP.Ensure the initial PEEP is ≤ 15 cmH_2_O. If PEEP is set at ≤ 15 cmH_2_O, the corresponding plateau pressure will not exceed 30 cmH_2_O.Increase PEEP in a stepwise manner every minute in steps of 4 cmH_2_O to a achieve Pi of 40–43 cmH_2_O.Reduce PEEP to 24, and then by decrements of 2 cmH_2_O, every 2 min, until the SpO_2_ begins to fall by no less than 2% of the maximum observed. Hold PEEP at this level and then increase PEEP to the maximum that was previously used for 1 min before returning to a PEEP level 2 cmH_2_O above the level when the SpO_2_ was first noted to have fallen (the decrements in 2 cmH_2_O will allow a PEEP selection between 16 and 24 cmH_2_O, which is within the high PEEP protocol from the ARDS Clinical Network study of high versus low PEEP [4].If there is no desaturation during the decremental phase of the SRM, reduce PEEP to 16 cmH_2_O; no further changes in PEEP are required.Return the patient to the previous ventilation mode.Adjust the DP to ≤ 15 cmH_2_O to give a V_T_ ≤ 6–8 ml/kg IBW. If the plateau pressure is > 30 cmH_2_O, adjust the DP so that V_T_ is to 4–6 ml/kg IBW and tolerate permissive hypercapnia. You may increase the respiratory rate up to 30 breaths/min provided there is no significant auto-PEEP causing breath stacking.Reduce the ETT cuff pressure to the previous level and re-set ventilator alarms to previous settings. Record ABGs 30–60 mins after the conclusion of the procedure.

## Ventilator dyssynchrony

Ventilator dyssynchrony occurs when a patient’s spontaneous respiratory efforts are not synchronised with the ventilator. This commonly causes agitation and respiratory distress; often described as “fighting the ventilator”. Dyssynchrony should be considered in patients with increased respiratory efforts, unexplained agitation, tachycardia, or sweating. Ventilator wave forms can be used to identify dyssynchrony.

In participants assigned to MBV, dyssynchrony will often cause large spikes in the elastance recordings. The CURE soft algorithm does not account for patient breathing efforts and “sees” inspiratory effort as a rapid reduction in lung elastance [32, 33]. In contrast, coughing, breath-holding, and other dyssynchronous efforts may cause an apparent increase in elastance [34]. Figure 2 shows an example of ventilator dyssynchrony in a pressure-controlled mode. Dyssynchrony may be seen as negative deflections (“M” waves) in the flow-time waveform, as shown in Fig. 2. In contrast the airway pressure may only be changed minimally by patient effort.

**Fig. 2 Fig2:**
[figure not shown]
An “M” wave is seen in the flow-time waveform (flow starvation), followed by a spontaneous (pressure-supported) breath

It is important to exclude reversible mechanical causes that might lead to patient distress and ventilator dyssynchrony. Endobronchial intubation, obstruction of a major bronchus or pneumothorax should be excluded.

Usually ventilator dyssynchrony can be managed by increasing sedation. However, in many cases it may be preferable to use intermittent muscle relaxants to fully control ventilation. It also may be helpful to trial the patient on assisted spontaneous breathing (ASB) to improve ventilation synchrony, if PEEP is ≤ 10 cmH_2_O and the FiO_2_ is ≤ 40%. However, caution should be exercised, lest the patient become exhausted (see “Weaning”).

## Weaning assessment

These guidelines are a pragmatic and consistent way to transition patients to ASB. Weaning is challenging and difficult to protocolise because there are many different factors to consider. For this reason, the weaning process is typically determined by clinical judgement. However, the guidelines presented here are set to ensure consistency of care.

ASB is considered when the participant’s condition is improving. They should preferably be afebrile, have resolution of the underlying processes that led to their ICU admission and improving gas exchange. They should have improving muscle strength, decreasing sedation requirements with an improving Glasgow Coma Score (GCS) and Richmond Agitation Sedation Score (RASS) between −3 and +1. Generally, the FiO_2_ should be ≤ 40% and PEEP ≤ 10 cmH_2_O.

If the following are substantially present, then participants may be transitioned to ASB:
Improving conditionMinute ventilation acceptable (VE) ≤ 0.2 L/kgFiO_2_ ≤ 40%SpO_2_ 93–95%pH ≥ 7.3Heart rate ≤ 120 beats/minLow vasoactive drug requirements (noradrenaline + adrenaline ≤ 10 mcg/min)

The following instructions or recommendations are used to guide transition to ASB:
Set mandatory respiratory rate (RR) at ≤ 10 cmH_2_O.Set pressure support (PS) at 10–15 cm cmH_2_O.Consider PEEP level.
Generally, keep PEEP at ≤ 10 cmH_2_O.PEEP maybe up to 15 cmH_2_O in obese participants or when the chest wall or abdominal elastance is increased.Monitor RR, HR and SpO_2_ over the next 30 min. If there is significant increase in distress, desaturation, or an increased oxygen requirement, the participant is reverted back to the previous controlled ventilation mode.If there is no significant deterioration, change the ventilation mode to ASB.If the participant is comfortable, you may reduce PEEP and PS after 12 h. Titrate PEEP and PS as clinically indicated by ≤ 2 cmH_2_O PEEP; PS should remain at ≥ 5 cmH_2_O. Reductions in PEEP and PS should be generally made between 0800 and 1800 hours.

### Observations during ASB

The following observations should be made:
Check RR, HR and SpO_2_ every 2 h:
If there are increases in heart rate, agitation, delirium, respiratory distress, minor desaturations, or increasing oxygen requirements (ΔFiO_2_ ≥ 10% or FiO_2_ ≥ 50%), check the patient and the ventilator;
i.Exclude patient conditions, e.g. endobronchial intubation, mucous plugging, pneumothorax etc.;ii.Optimise analgesia/sedation and patient position;iii.Consider increasing
Pressure support up to 15 cm;Expiratory time for triggering (e.g. adjusting E sens up to 50% on the PB840 ventilator);Triggering sensitivity;If the FiO_2_ is ≥ 50% or the FiO_2_ has increased by ≥ 10% in the previous 2 h, consider adjusting PEEP up (or down) by ≤ 2 cmH_2_O. Consider repositioning the patient and optimising sedation;If secretions are obstructing large airways, or there are significant regions of consolidation, these conditions are unlikely to respond to increases in PEEP and increases in PEEP may impair oxygenation. Thus, if the PEEP is > 10 cmH_2_O, consideration should be given to reducing it;If the aforementioned measures do not improve oxygenation, re-sedate and revert back to the previous controlled ventilation mode (Bi-Level or PC-SIMV+ or equivalent);If the oxygenation has not improved after 12 h on controlled ventilation, or there is an unanticipated new problem causing deterioration, the participant should return to their previously assigned ventilation arm (MBV or SPV), e.g.:
iv.New lung injury/de-recruitment/aspiration/sepsis.v.Haemodynamic instability.vi.Need to return to the operating room or to undergo invasive procedure.If there is continual improvement, proceed towards separation from mechanical ventilation (extubation or continuous positive airway pressure (CPAP) via a tracheostomy).

## Patient enrolment and data management

A simplified flow chart of the patient enrolment process can be found in Additional file 1. All study data, including ventilation data, patient and family/friend consent, SAE reports and other documentation will be stored in a repository.

### Consolidated standards of reporting trials (CONSORT)

Figure 3 shows the CONSORT diagram for the CURE RCT.

**Fig. 3 Fig3:**
[figure not shown]
Consolidated standards of reporting trials (CONSORT) diagram for the CURE randomized controlled trial (RCT). P/F, partial pressure of arterial oxygen/fraction of inspired oxygen; PEEP, positive end-expiratory pressure; FiO_2_, fraction of inspired oxygen; COPD, chronic obstructive pulmonary disease; PAO_2_, partial pressure of arterial oxygen; LoMV, length of time of mechanical ventilation; VFD, ventilator-free days; SPO_2_, oxygen saturation; ECMO, extracorporeal membrane oxygenation

### Data acquisition and management

Patients recruited into the CURE RCT will have the following data collected.

#### Patient demographic and history

The following data will be collected:
Patient gender, height, weight and ethnicityPrimary patient diagnosis contributing to ARDS or impaired lung functionSecondary patient diagnosis contributing to ARDS or impaired lung functionRelevant past medical history, e.g. smoking, medication, cardiovascular diseaseChest x-ray score derived by the Murray Index [35]

#### Patient mechanical ventilation data

Data on patient airway pressure and flow generated from the mechanical ventilator will be recorded using the CURE software (CURE Soft.) provided with the RCT. The patient data are backed up regularly to external storage with encryption applied using VeraCrypt encryption software [36].

#### Other patient information

The following information will be collected:
Demographic data
Age, weight, heightEthnicityAcute Physiology and Chronic Health Evaluation (APACHE) II and IIIJ, Simplified Acute Physiology Score (SAPS) II, Australian and New Zealand Risk of Death (ANZROD) from the ANZICS CORE databaseWaveform data from physiological monitors including:
SpO_2_ - used to detect desaturation eventsBlood pressureHeart rateEnd-tidal CO_2_Arterial blood gases:
Measured at least twice dailyBefore and after any RM_Max_ or PUMPRoutine biochemical analysis (up to daily)
Electrolytes, urea, creatinine, glucose, liver testsFull blood countPatient’s findings on radiology (chest x-ray and computed tomography (CT))Patient position during MV (to account for data variation resulting from changes in patient position)Rescue therapies: (i) prone positioning, (ii) nitric oxide (iii) ECMOLength of time of mechanical ventilation (LoMV) or ventilation-free daysAmount of sedation - to account for possible data variation resulting from use of different sedativesDuration of ICU stayFrequency and duration of renal support therapiesAll causes of ICU, hospital and 90-day mortality

#### Blood samples

No person or authority will have access to the participant’s blood. The blood samples are not stored. They are discarded and incinerated as soon as practicable, in accordance with NZS 4304:2002 “Healthcare Waste Management”.

#### Data management

All CURE RCT data will be stored at the University of Canterbury (UC). All paper forms (patient sheets, consent forms, etc.) will be scanned and stored at the UC. All electronic data will be stored in double-encrypted repository and only the participating researchers have access to it. Currently there are no plans for sharing the data, but if requested, data may be shared. Participants in the study can request their copy of data.

The data will be backed up weekly and again, once the participant has finished the trial and left the hospital. This task will only be performed by the participating researchers. Any protocol variations will be followed up and noted. The CURE RCT will store data for 20 years.

### Study outcome

The trial will utilise a primary composite end point incorporating the AUC of the P/F ratio over the period of MV. Every participant in the intervention (MBV) group is compared with every participant in the control (SPV) group. Test statistics will be calculated using the one-sided Wilcoxon rank sum test at alpha of 0.05. If results show no statistically significant difference between the intervention and control, it will result in the rejection of the intervention treatment as a standard of care and thus, the secondary clinical outcome assessments will include the number of desaturation events measured as peripheral capillary oxygen saturation < 90%, LoMV, VFD for 28 days, the quality of mechanical ventilation care measured as the AUC of SpO_2_/FiO_2_ and chest x-ray index scores over time. The test statistic will be calculated using the one-sided Wilcoxon rank sum test at alpha of 0.05.

A difference in the primary outcome will show the impact of MBV compared to SPV. No difference would show that enhanced, model-based metrics of the patient-specific condition have no effect on patient-centred or clinical outcomes. Either outcome will yield clinical guidance.

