Level 4 Method of aggregation	Comparisons of the of means of AUC		Comparisons of the means of number of days	Comparisons of the means of VFD	Comparisons of the means of length of stay		Comparison on number of 90-day mortality	Comparison of index scores over time	Comparison of rescue therapies used.

*P/F* partial pressure of arterial oxygen/fraction of inspired oxygen, *SPO*_*2*_ oxygen saturation, *MV* mechanical ventilation, *FiO*_*2*_ fraction of inspired oxygen

A difference in primary and secondary outcomes will show the impact of MBV compared to SPV. No difference would show that enhanced, model-based metrics of patient-specific condition have no effect on patient-centred or clinical outcomes. Either outcome will yield clinical guidance.

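### A non-significant one-sided test on oxygenation is to be read as showing that model-based ventilation has no effect on clinical outcomes

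*Protocol article*

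**What the plan says.** In the Protocol article, the Study outcome section defines the primary outcome: "The trial will utilise a primary composite end point incorporating the AUC of the P/F ratio over the period of MV". It then fixes the test: "Test statistics will be calculated using the one-sided Wilcoxon rank sum test at alpha of 0.05".

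The consequence of missing significance is written in advance: "If results show no statistically significant difference between the intervention and control, it will result in the rejection of the intervention treatment". The sentence goes on to specify rejection as a standard of care. A connective then leads straight into the secondary outcomes: "thus, the secondary clinical outcome assessments will include the number of desaturation events", followed by LoMV, VFD, the AUC of SpO2/FiO2 and chest x-ray scores. The one-sided Wilcoxon test at 0.05 is then stated again.

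The next paragraph gives the interpretation: "No difference would show that enhanced, model-based metrics of the patient-specific condition have no effect on patient-centred or clinical outcomes". A near-identical sentence stands below Table 1 in Study design and setting: "No difference would show that enhanced, model-based metrics of patient-specific condition have no effect on patient-centred or clinical outcomes". There it follows a sentence about a difference in primary and secondary outcomes together.

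The article gives no equivalence margin, smallest important difference or confidence-interval rule. Its only power statement, in Sample size study, concerns LoMV at a two-sided 5% level.

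**The concern.** A superiority test that misses significance has not shown that there is no effect. It may simply be imprecise. The plan makes the two equivalent, in three ways that matter.

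- **Inconclusive results.** An estimate that favours MBV, with an interval reaching effects worth having, would be reported as no effect.
- **Worse oxygenation.** A test that looks only for benefit is also non-significant when the intervention does worse, so harm and absence of effect share one label.
- **Reach of the conclusion.** In Study outcome the null is on an oxygenation AUC, but the conclusion is about patient-centred and clinical outcomes. LoMV, VFD and mortality are different variables, and a null on oxygenation cannot settle them.

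A lesser problem is the connective between the rejection clause and the secondary outcomes. It can be read as saying that secondaries are tested because the primary failed. That conflicts with the abstract and with Study design and setting, which list secondary outcomes without any condition.

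**Working it through.** **Inputs from the Protocol article.** 160 per arm; 25% reduction in median LoMV; power 0.80; two-sided 5% (Sample size study). 1:1 allocation (Randomisation and blinding). One-sided Wilcoxon at 0.05 and five named secondary outcomes (Study outcome). The direction tested is taken to be benefit of MBV.

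**1. The plan's own figure.** No distribution for LoMV is given, so 160 per arm cannot be reproduced directly. Back-solving on the log scale with the rank-test efficiency factor:

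n per arm = (π/3) × 2 × (1.960 + 0.842)² × σ² / (ln 0.75)², with |ln 0.75| = 0.288.

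Setting n = 160 gives σ of about 0.90. A 4,000-run lognormal simulation at σ = 0.90 gave power 0.806. Assumed σ of 0.7 to 1.2 gives 93 to 274 per arm on the t-test formula (without π/3). So 160 is plausible for LoMV, but it says nothing about power for the AUC of P/F.

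**2. What a non-significant primary result can contain.** Let θ be the probability that an MBV patient has a higher AUC than a control patient; θ = 0.50 means no difference.

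- Null SE = √[(160 + 160 + 1) / (12 × 160 × 160)] = √(321 / 307,200) = 0.0323.
- 95% half-width = 1.96 × 0.0323 = 0.063.
- Observed θ = 0.55: z = 0.05 / 0.0323 = 1.547, one-sided p = 0.061, so non-significant.
- Approximate 95% CI = 0.55 ± 0.063 = 0.49 to 0.61.
- Value detectable with 80% power at two-sided 5%: 0.50 + (1.960 + 0.842) × 0.0323 = 0.59, inside that interval.

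**3. How often a real benefit would be called no effect.** For an assumed true shift of d standard deviations, P(non-significant) = 1 − Φ(d × √(80 × 3/π) − 1.645).

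| Assumed true benefit (SD) | P(non-significant) |
|---|---|
| 0.1 | 0.78 |
| 0.2 | 0.46 |
| 0.3 | 0.16 |
| 0.4 | 0.03 |

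**4. Harm.** For d = −0.2 the same formula gives 0.9997. A true worsening of oxygenation of 0.2 SD or more would almost always be labelled no difference.

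**5. Five secondaries at one-sided 0.05, if all are tested so.** With every null true and independence: 1 − 0.95⁵ = 0.226. A simulation of 400,000 draws with an assumed common correlation gave:

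| Assumed correlation | At least one of five | Same, given a non-significant primary |
|---|---|---|
| 0 | 0.226 | 0.227 |
| 0.3 | 0.194 | 0.179 |
| 0.5 | 0.166 | 0.143 |
| 0.8 | 0.117 | 0.080 |

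The independent figure is a ceiling in practice: Table 1 defines VFD as 28 days minus days of MV, so VFD and LoMV largely overlap.

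**The case against.** Several points can fairly be made for the plan.

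- **Rejection is only as a standard of care.** Declining to adopt a procedure that has not shown superiority is a conventional decision, and Background calls this a phase-2 trial. If MBV is harmful, non-adoption is also the right action. This stands. The defect is the inference drawn, not the decision to withhold adoption. What it does not answer is the statement that a null result shows no effect.
- **Harm is partly covered elsewhere.** Stopping rule sets a mortality boundary with cumulative alpha 0.025, and the DMC reviews serious adverse events and can stop the trial. This stands for mortality and safety events. It does not give a conclusion of harm on oxygenation, which is where the one-sided primary test is blind.
- **The sentence below Table 1 covers primary and secondary outcomes together.** So the step from an oxygenation null to clinical outcomes is a fault of Study outcome only. The no-effect inference is common to both places.
- **Secondaries.** A reader might infer that the plan reverses gatekeeping and lets a significant secondary rescue a failed primary. The text does not support that. The linking words are garbled, the other lists are unconditional, it is only inferred that every secondary is tested at 0.05, and nothing lets a secondary overturn the rejection. A multiplicity scheme is also commonly left to an analysis plan, so its absence is no finding.

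**Conclusion.** The interpretive error is real and is fixed in the text: Study outcome equates a non-significant one-sided test on the AUC of P/F with no effect on patient-centred or clinical outcomes, and Study design and setting repeats the inference for all outcomes together. Nothing else in the article cures it, and an analysis plan could only contradict it.

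Its size: an estimate of 0.55 at 160 per arm would count as no effect although its interval reaches 0.59, and an assumed true benefit of 0.2 SD would be so labelled 46% of the time. These figures use normal approximations without ties and the null standard error. The 0.59 is a generic rank-sum value, since the protocol states no power for this outcome.

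On the secondaries, the finding is ambiguous wording that needs reconciling with the unconditional lists. If all five were tested at one-sided 0.05, the chance of at least one false positive is at most about 23%, and about 12% to 19% at assumed correlations of 0.8 to 0.3.

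**What to change.** - Delete the no-effect sentences in Study outcome and below Table 1.
- Replace the automatic rejection clause with a conclusion from the two-sided 95% CI for the primary outcome: benefit, harm or inconclusive. Allow a claim of no important effect only if the interval excludes a margin stated in advance.
- Remove the connective that ties the secondary outcomes to a failed primary. State that secondaries are reported with estimates and CIs whatever the primary shows, and are supportive only if the primary is not met.

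The cost is text editing; these changes leave data collection and sample size as they are, and Trial status says recruitment had not begun. The sponsor gives up a firm negative statement: a null result will support a weaker conclusion than the plan now promises.
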